### Inclusion criteria

Participants who meet all the following requirements will be allowed to enrolWomen aged 45–70 yearsPatients who meet the diagnostic criteria for PMOPPain occurs mostly with the hips, lower back and ribs, and is of slow onsetA brittle fracture occurs with only slight external forceThere is an obvious tender point on the lower back or there is a large area of tendernessScoliosis, kyphosis and other deformities existDXA (dual-energy x-ray absorptiometry) is used to detect a femoral-neck bone-mineral density lower than − 2.5. Severe osteoporosis is accompanied by two or more fracturesImaging examination showed obvious osteoporosis or a fragility fractureNon-secondary osteoporosis is presentPatients who meet the “atrophic debility of bones” in the Chinese medicine diagnostic criteriaNatural menopause for more than 1 yearOther medications or other related interventions for PMOP were not received within 4–6 monthsPatients voluntarily provided informed consent, and willingly signed the informed consent

### Exclusion criteria

Participants meeting any of the following criteria will be excluded:1. Except for women with abnormal lumbar anatomy (such as severe scoliosis)Exclude related endocrine disorders (such as diabetes, hyperthyroidism, hypothyroidism, thyroid cysts, etc.) that can cause secondary osteoporosisAfter uterine or ovarian ablation surgeryConcomitant with diseases such as rickets, rheumatoid arthritis or other diseases that affect the dynamic balance of bone metabolismIn the past 3 months, the participant has taken drugs that can interfere with bone metabolism (such as glucocorticoids, calcitonin, estrogens, etc.);Female patients with severe underlying diseases and mental illness who are unable to cooperate with treatment research programsDrug or alcohol dependency/misuseThose who had received acupuncture treatmentThose participating in other clinical trials

### Interventions

Both the OA and SA groups will receive acupuncture sessions for a total of 3 months. All the patients will receive herbal medicine twice a day for 3 months. The same physician (the Professor of Acupuncture in Yunnan Provincial Hospital and Traditional Chinese Medicine, who has 20 years of work experience) will slightly adjust the formula each week depending on the changes of the symptoms, pulse, and tongue coating of the patients (main herbal formula components are shown in Table 1). During the trial, patients will be classified by pattern differentiation: (1) spleen-kidney *Yang* deficiency will be given Yougui Pill; (2) liver-kidney *Yin* deficiency will be given Zuogui Pill; and (3) kidney deficiency and blood stasis will be given Bushen Huoxue decoction. Participants will be given all the herbs from the same hospital and the physician will instruct them how to decoct.

**Table 1 Tab1:** Main herbal formula selection

Pattern	Formula	Composition
Spleen-kidney *Yang* deficiency	Yougui Pill	radix rehmanniae preparata, cortex cinnamomi, cornu cervi degelatinatum, rhizoma dioscoreae, fructus corni, fructus lycii, radix angelicae sinensis, cortex eucommiae, semen cuscutae, radix morindae officinalis, rhizoma drynaria, rhizoma sparganii
Spleen-kidney *Yin* deficiency	Zuogui Pill	radix rehmanniae preparata, rhizoma dioscoreae, fructus lycii, fructus corni, radix achyranthis bidentatae, deerhorn glue, deerhorn glue, radix morindae officinalis
Kidney deficiency and blood stasis	Bushen Huoxue decoction	radix rehmanniae preparata, semen cuscutae, cortex eucommiae, fructus lycii, radix angelicae sinensis, fructus corni, cistanches herba, commiphora myrrha, radix angelicae biseratae, radix angelicae sinensis

According to the OA and moxibustion [15], and taking opinions from Chinese acupuncture experts, the essential acupuncture points selected are as follows: BL11 (Dazhu), BL23 (Shenshu) and ST36 (Zusanli). The additional individualized acupuncture points will be chosen by the practitioners according to the patterns of identification: (1) kidney *Yang* deficiency will have added DU04 (Mingmen), GB34 (Guanyuan); (2) spleen-kidney *Yang* deficiency will have added DU04 (Mingmen), GB34 (Guanyuan); (2) liver-kidney *Yin* deficiency will have added SP06 (Sanyinjiao), LU11 (Taixi); (3) kidney deficiency and blood stasis will have added SP06 (Sanyinjiao), BL17 (Geshu) (Table 2). A placebo device [16] will be applied in both groups for better implementation of blinding. The schematic diagram of the acupuncture treatment is shown in Fig. 2.The acupuncture treatment in both groups will take 30 min per session, twice per week. Three months is the duration of a course of treatment, for a total of one course .

**Table 2 Tab2:** Acupuncture point selection

Point	Location
BL11 (Dazhu)	In the spinal region, under the spinous process of the 1st thoracic vertebra, 1.5 cun lateral to the posterior midline
BL23 (Shenshu)	1.5 cun beside the spinous process of the 2nd lumbar vertebra
ST36 (Zusanli)	At the anterior aspect of the leg 3 cun inferior to ST35 (Dubi) on the line connecting ST35 (Dubi) to ST41 (Jiexi)
DU04 (Mingmen)	Between the spinous processes of the 2nd and 3rd lumbar vertebrae
GB34 (Guanyuan)	On the lower abdomen at the anterior midline, 3 cun below the umbilicus
SP06 (Sanyinjiao)	On the tibial aspect of the leg posterior to the medial border of the tibia, 3 cun superior to the prominence of the medial malleolus
LU11 (Taixi)	On the posteromedial aspect of the ankle in the depression between the prominence of the medial malleolus and the calcaneal tendon
BL17 (Geshu)	Under the spinous process of the 7th thoracic spine on the back, 1.5 cun lateral to the midline

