**Fig. 1 Fig1:**
[figure not shown]
Study flow chart

Participants who voluntarily sign the informed consent, and who are eligible for this study, will be assigned randomly to one of two groups (the acupuncture group or the SA group) in a 1:1 allocation. On the consent form, participants will be asked if they agree to the use of their data should they choose to withdraw from the trial. Participants will also be asked for permission for the research team to share any relevant data with people from the Dali University who are taking part in the research or from regulatory authorities, where relevant. The study participants were recruited competitively from two sites of the Acupuncture and Moxibustion Department of Yunnan Province Hospital of TCM and the First Affiliated Hospital of Dali University. A total of 104 postmenopausal women with osteoporosis were recruited via broadcast media, newspapers, posters, and the Internet homepages of the participating hospitals, as well as via advertisements placed in nearby welfare centers.

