### Randomization and allocation concealment

For randomization, an independent, blinded statistician will generate random numbers using the SAS randomization program (version 9.4; SAS Institute, Inc., Cary, NC, USA). The manufacturer will supply the hospital with investigational treatments in consecutively numbered drug containers with identical packaging to conceal treatment allocation. Blinded researchers in each hospital will enroll and assign participants to one of the two study groups.

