### Sample size and blinding

According to the preliminary research [15], we hypothesize that the effective rate after OA is 77.8% and the effective rate after SA is 50%. The equation that we used for this was *α* = 0.05, *β* = 0.20 and we determined that a sample size of 42 patients in each group would be sufficient to detect the statistical difference between the two groups, allowing for a 20% withdrawal rate. We will plan to enroll a total of 104 participants with 52 participants in each group. According to the random number sequence generated by computer, the patients will be randomly divided into either the OA group or the SA group in a 1:1 ratio.

The participants, outcome assessors, study monitors, data managers, and statisticians will be blinded to treatment allocation. If possible, the study participants will be advised to avoid discussing the investigational treatments with other participants. Blinding will be maintained until the 104 participants have completed the study. The success of double-blinding will be assessed at the final visit. Due to the special nature of acupuncture, acupuncturists cannot be blinded to the treatment. The database will then be locked. An emergency code for each individual has been provided to the study researchers and will be disclosed only if it must be known whether a patient is receiving acupuncture treatment or SA in order to manage a serious adverse event.

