### Data analysis

The analysis data set will consist of an intention-to-treat data set, a per-protocol (PP) data set, and a safety data set. The intention-to-treat data set will include all subjects assigned to each group. The PP data set will include only participants who adhered to the study protocol and completed the clinical study. The minimum compliance rate for participants taking the acupuncture treatments in the PP data set is 80%. The safety data set will include any participants who were randomly assigned to, and received, at least 1.5 months of the acupuncture treatments. The intention-to-treat analysis will be the primary analysis and will be compared with the PP analysis in a sensitivity analysis. The last-observation-carried-forward method will be used to manage missing data.

All collected data results were compiled using the SPSS 21.0 statistical software package, and collated, checked and statistically analyzed. The comparison between the data groups was performed by using a *χ*^2^ test, and the measurement data was consistent with the normal distribution and the homogeneity of the variance. The mean ± standard deviation ($$\overline{\mathrm{x}}\pm \mathrm{S}$$) indicates that the rank-sum test is used for comparison between grade data sets that do not satisfy the normal distribution and the homogeneity of the variance. *P* < 0.05 was significant for the difference. The variance analysis will be performed for the difference between the two groups and within the group. We will perform a regression analysis to examine the causal relationship between the E2, TAC and β-catenin, and the primary outcome. The statisticians who are independent of the research team will conduct the data analysis.

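### TCM pattern decides the herbal formula in both arms, yet the protocol does not fix it before allocation, and the stated analysis names neither pattern nor hospital

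*Protocol article*

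**What the plan says.** **Role of pattern.** The Interventions section states "During the trial, patients will be classified by pattern differentiation" and ties each of three patterns to its own herbal formula, given in both arms. The paragraph on point selection has practitioners choose the additional points by pattern. The section on the OA group makes skin-needle stimulation stronger for one type than for the others.

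**Who knows the arm.** The section on sample size and blinding says acupuncturists cannot be blinded. One physician adjusts the formula weekly. The note on TCM syndrome scores has one professor rescoring weekly and adjusting both acupuncture and herbs. Whether that person knows the arm is not stated.

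**Allocation and sites.** A statistician "will generate random numbers using the SAS randomization program", in a 1:1 ratio, with no stratification factor named. Under Study design, "The study participants were recruited competitively from two sites".

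**Analysis.** The Data analysis section says: "The variance analysis will be performed for the difference between the two groups and within the group". The only regression named uses E2, TAC and β-catenin. Pattern and hospital do not appear.

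**Visit schedule.** Table 3 has no row for pattern. A row for TCM syndrome is ticked at month −1, before allocation at month 0.

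**The concern.** The herbs are meant to be a common background, so that the arms differ only in real versus sham acupuncture. That holds only if a woman's formula is chosen independently of her arm. If pattern is assigned or revised once the arm is known, or once acupuncture has begun to change her symptoms, the herb mix can differ between arms for reasons other than chance. The BMD difference would then no longer isolate the acupuncture component.

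The second consequence is for analysis. A pattern recorded after allocation cannot safely serve as a baseline covariate. If no earlier value was recorded, no later analysis plan can recover it. This is why the timing of classification belongs in the protocol.

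The absence of pattern and hospital from the stated model is a lesser matter of precision.

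**Working it through.** **1. Timing, by comparing sections.**
- The Interventions text says only that classification occurs in the course of the trial. Enrolment is part of the study period in Table 3, so this could mean before or after allocation.
- The TCM syndrome tick at month −1 does not settle it. If that row means pattern, a pre-allocation value exists. If it means the symptom scale in Table 5, it gives severity points and assigns no pattern. Table 5 is the scale the text attaches to TCM syndrome scores, so the second reading is more likely, but it is not stated.
- No section rules out classification after allocation.

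**2. The lists of patterns do not agree.**

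| Place | Patterns named |
|---|---|
| Interventions, herb text | spleen-kidney Yang; liver-kidney Yin; kidney deficiency with blood stasis |
| Table 1 | spleen-kidney Yang; spleen-kidney Yin; kidney deficiency with blood stasis |
| Interventions, point selection | kidney Yang; spleen-kidney Yang; liver-kidney Yin; kidney deficiency with blood stasis |
| OA group, skin needle | blood stasis with Qi stagnation, versus all others |

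A covariate needs one list.

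**3. The plan's own number.** The plan concludes that "a sample size of 42 patients in each group would be sufficient", "allowing for a 20% withdrawal rate", from effective rates of 77.8% and 50%, α = 0.05 and β = 0.20. Assuming a two-sided test with unpooled variance:

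n = [0.778 × 0.222 + 0.5 × 0.5] × (1.960 + 0.842)² / 0.278² = 0.4227 × 7.849 / 0.07728 = 42.9 per arm.

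Then 42 / 0.8 = 52.5, against 52 per arm enrolled. The figure reproduces within rounding. It is built on a responder rate and gives no SD for BMD and no variance explained by pattern or hospital, so the value of adjustment cannot be derived from it.

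**4. Cost and gain of adjustment (R² assumed).** Let R² be the share of outcome variance explained by pattern (2 df) and hospital (1 df). With N = 104 and k = 3 added terms, the variance of the treatment difference changes by approximately

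(1 − R²) × (N − 3)/(N − 3 − k) = (1 − R²) × 101/98.

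| R² | Ratio | Equivalent change in N = 104 (104/ratio − 104) |
|---|---|---|
| 2% | 0.98 × 1.0306 = 1.010 | about −1 |
| 5% | 0.95 × 1.0306 = 0.979 | about +2 |
| 15% | 0.85 × 1.0306 = 0.876 | about +15 |

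Break-even is at R² = 3/101, about 3%.

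**5. Chance imbalance (shares assumed).** For an unstratified 52:52 split:
- A pattern held by one third of women: the SD of the between-arm difference is 9.3 percentage points, and the probability of a gap of at least 10 points is 0.21. For a gap of that size in any of three equally common patterns, it is 0.47.
- Two equal hospitals: the SD is 9.9 points and the probability is 0.33.

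These are ordinary chance differences under valid randomisation. They describe variation that adjustment can remove, not bias.

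**The case against.** The strongest reply is that this is a journal article. Strata, block scheme and model covariates are commonly left to the full protocol or analysis plan, neither of which is shown. Nothing in the randomisation or Data analysis text excludes them. That stands, so the absence of stratification is not pressed as a defect, and the adjustment part is a modest recommendation. Its benefit rests on assumed figures, and its sign changes at about 3% of variance explained.

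Three stronger readings are tempting, and the document does not support them:

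- *Classification is known to follow allocation.* The timing is unspecified, and enrolment may count as part of the trial. Only the acupuncturists are stated to be unblinded; the status of the physician adjusting the herbs is not given.
- *Hospital also sets the formula, points or stimulation.* It does not. All herbs come from one hospital, one physician adjusts the formula, and techniques are standardised between practitioners. Hospital matters only as an ordinary two-site factor.
- *Randomisation without these factors biases the comparison, and blocking within hospital would cure pattern imbalance.* Unstratified allocation costs precision only, and blocking within hospital does nothing to balance pattern.

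The timing gap survives these replies. A site could follow the article exactly, choose an active co-treatment after the arm is known, and hold no baseline record of pattern. That is a rule left open at a point where it affects the comparison.

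**Conclusion.** The point holds in limited form. Pattern governs the herbs in both arms and part of the acupuncture procedure, its assignment is not fixed before allocation, and unblinded practitioners act on it. This opens a route for arm to influence co-treatment and leaves no guaranteed baseline pattern for analysis. Whether that route is used, and how far it would move BMD, cannot be determined from the document.

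The precision argument is secondary. On assumed values of 2% to 15% of variance explained, adding both factors ranges from a 1% loss to a 12% reduction in variance. The correction is worth making because it is cheap and, for the timing part, cannot be made afterwards.

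**What to change.** 1. Reconcile the pattern lists in the Interventions text, Table 1, the point-selection paragraph and the OA group section into one list used throughout.
2. State who classifies pattern. Record it in a dated field at the enrolment visit, before that woman's allocation is opened, and keep the value unchanged for analysis. Record later treatment adjustments separately; this change does not alter them or how treatment is chosen.
3. Add enrolment pattern (2 df for three patterns) and hospital (1 df) as fixed effects to the between-group model for BMD and the continuous secondary outcomes. A reconciled list of four patterns would add one further df.
4. Recruitment was under way when the article was submitted. For women already randomised, use pattern as a baseline covariate only where a dated record precedes allocation.

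The cost is one form field, two model terms and 3 df: about 1% in variance if the factors explain only 2%, and nothing once they explain about 3%. The sample size need not change.

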**Fig. 2 Fig2:**
[figure not shown]
Schematic diagram of the acupuncture device

### Overall adjustment acupuncture (OA) group

Acupuncture manipulation will be applied to the acupoints of the body until the patient achieves *Qi*, including soreness, soreness and distension, pain, numbness, tingling and even comfort. Huatuo brand needles (0.25 mm × 40 mm) are manufactured by the Suzhou Medical Device Company in Suzhou, Jiangsu Province, China. After the patient achieves *Qi* in Shenshu and Zusanli, warm acupuncture will be used, the 2 cm-long moxa-stick will be fixed on the handle of the needle and lit at the root of the needle and allowed to burn for 20 min.

The parameters of the skin-needle are set as follows: *Qixing* needle; tapping along the first side line of the urinary bladder meridian in the back; moderate stimulation will be applied for blood stasis and *Qi* stagnation type, until redness of the skin and petechiae are observed in the tapping area; mild stimulation is used for the other syndromes until redness in the skin is observed.

The parameters of the cupping are set as follows: moving cupping; smear the tapping spot evenly with Vaseline and move the cup along the first lateral line of the urinary bladder meridian, back and forth until red-blood stasis appears on the skin, according to the patient’s tolerance (feeling comfortable, without obvious pain). Retaining cupping: leave the cup for 8 to 10 min in Dazhui, Shenshu, and a severely painful area.

### Sham acupuncture (SA)group

The procedure and duration of treatment in the SA group will be identical to the OA group except for the needles (0.25 × 25 mm with a blunt tip, manufactured by Suzhou Medical Device Company in Suzhou, Jiangsu Province, China). The *Qixing* needle tips are wrapped in cotton (shown in Fig. 3) are blunt-tipped and there will be no skin penetration or manual stimulation, but at the same time cupping is applied to the skin with a small negative pressure compared to that in the OA group (show in Fig. 4).

**Fig. 3 Fig3:**
[figure not shown]
Schematic diagram of a skin needle

**Fig. 4 Fig4:**
[figure not shown]
Schematic diagram of cupping

#### Practitioner background

The OA and SA treatments will be handled by acupuncturists who are registered and possess the TCM practitioner qualification certificate and who are specialized in acupuncture with more than 3 years of clinic experience. They will have studied acupuncture for more than 10 years and graduated from a TCM university. All operators will be trained in the overall adjustment of the needling procedure and will be advanced qualified, and will undergo intensive and customized training for a full understanding of the SA procedure and for using a sham needle device. The techniques for the entire treatment procedure will be standardized between practitioners.

### Concomitant and forbidden treatments

Drugs that have been taken for an indication other than osteoporosis for more than 30 days before the screening visit may be continued during the study period. Continuation of the same doses of health supplements, such as calcium or vitamin D, are permitted in this trial only if they have been taken continuously in the 3 months before the screening visit. Prohibited drugs include agents that can affect bone mineral density (BMD), such as other medications for osteoporosis, steroids, carbamazepine, phenytoin, phenobarbital, heparin, warfarin, thyroid hormones, gonadotropin-releasing hormone agonists, depot-medroxyprogesterone acetate, anticancer drugs, cyclosporine A, antidepressants, aluminum-containing antacids, aromatase inhibitors, antituberculosis drugs, thiazolidinedione, proton-pump inhibitors, antiretroviral drugs, and thiazide diuretics. Participants who have taken or are still taking any of these medications will be withdrawn from the study.

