### Data management

Researchers who have read and understood the standard operating procedures will obtain written consent and collect and manage the study data from the participants, who will be given ongoing encouragement to complete the study. They are telephoned in advanced of each visit and the importance of taking the investigational treatments at the correct times is reinforced. If a participant needs to be withdrawn from the study, the scheduled tests are still performed at the final study visit if the participant is agreeable. If a follow-up investigation is required, researchers will contact the participant by telephone as necessary. After the end of the trial, data entry will be by double entry, and matching will be conducted after inconsistent data has been reviewed. When the data is matched, a data clarification form will be completed and validated.

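### The concomitant-drug rules overlap without a stated precedence or a usable look-back, and the penalty is withdrawal from the study, which can leave only a baseline BMD to carry forward

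*Protocol article*

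**What the plan says.** All references are to the Protocol article.

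- **Concomitant and forbidden treatments, permission:** "Drugs that have been taken for an indication other than osteoporosis for more than 30 days before the screening visit may be continued". No exception is attached.
- **Same section, prohibition:** "Prohibited drugs include agents that can affect bone mineral density (BMD), such as other medications for osteoporosis, steroids, carbamazepine, phenytoin, phenobarbital, heparin, warfarin". The list goes on to thyroid hormones, antidepressants, proton-pump inhibitors, thiazide diuretics and others.
- **Same section, consequence:** "Participants who have taken or are still taking any of these medications will be withdrawn from the study".
- **Inclusion criteria:** no other treatment for postmenopausal osteoporosis (PMOP) within 4–6 months.
- **Exclusion criteria:** no drug that interferes with bone metabolism in the past 3 months; glucocorticoids, calcitonin and estrogens are the examples.
- **Data management**, on a withdrawn participant: "the scheduled tests are still performed at the final study visit if the participant is agreeable".
- **Data analysis:** the intention-to-treat set holds every woman assigned and is primary; the per-protocol set is a sensitivity analysis. "The last-observation-carried-forward method will be used to manage missing data".
- **Primary outcome:** lumbar (L1–L4) BMD, measured before and after treatment.

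**The concern.** Many drugs on the prohibited list are ordinarily taken for conditions other than osteoporosis, so the permission and the prohibition cover some of the same women. The text does not say which prevails. The withdrawal sentence reaches past as well as current use without a time limit, while the two eligibility criteria have limits of their own, one of them a range.

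Two things are at stake. The first is who is enrolled: two sites recruit competitively, and each must decide how to read these sentences. The second is who is followed: the penalty ends participation in the study, not merely study treatment, and it is addressed to participants rather than to women at screening. A drug deviation after randomisation can therefore put the end-of-treatment BMD at risk.

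**Working it through.** **1. The rules applied to the same women**

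The cases are illustrative.

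| Woman | Permission | Withdrawal sentence | Inclusion (4–6 months) | Exclusion (3 months) |
|---|---|---|---|---|
| A. On warfarin for another condition for two months before screening, continuing | May continue | Withdrawn | Not concerned | Unclear: the criterion gives examples and does not refer to the prohibited list |
| B. Took a listed drug for another condition, stopped 12 months before screening | Not concerned | Withdrawn if past use is read literally; not if only use during the study is meant | Passes | Passes |
| C. Took estrogen for PMOP, stopped 5 months before screening | Not concerned | Depends on the reading, as for B | Fails at 6 months, passes at 4 | Passes |
| D. Took estrogen for PMOP, stopped 3.5 months before screening | Not concerned | Depends on the reading, as for B | Fails at either end | Passes |

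A shows the conflict inside one section. C shows that a range cannot classify a woman who falls within it; the Introduction describes estrogen as a therapy for PMOP, so both windows apply to her. D shows that the two eligibility windows can be applied together: she is ineligible, because a woman must meet every inclusion criterion and no exclusion criterion.

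**2. What follows withdrawal after randomisation**

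- She stays in the intention-to-treat set.
- She is offered the scheduled tests at the final visit. If she accepts, her BMD is observed.
- If she declines, the last observation is used. The Primary outcome section gives only a before and an after measurement, and Table 3 marks no BMD in the treatment months. The last value is then the baseline value:

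  change = carried-forward BMD − baseline BMD = baseline BMD − baseline BMD = 0.

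The Outcome measures section speaks generally of a mid-treatment collection. If BMD were scanned then, that value would be carried forward instead; neither the Primary outcome section nor Table 3 says that it is.

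The consent form is also relevant: "participants will be asked if they agree to the use of their data should they choose to withdraw from the trial". That wording covers women who choose to leave, and does not clearly cover women removed under the drug rule.

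**3. Effect on the comparison**

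Let w be the share of an arm that is withdrawn and unscanned, and μ the mean change the arm would show if all were scanned. Assume that unscanned women would have had the same mean change as the others.

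- Analysed difference = (1 − w_OA)·μ_OA − (1 − w_SA)·μ_SA.
- With equal w this is (1 − w)·(μ_OA − μ_SA).

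The article gives no value for w. As an assumption only: 5%, 10% or 20% in both arms (2.6, 5.2 or 10.4 of 52 women) multiplies the difference by 0.95, 0.90 or 0.80. With unequal w the result can move either way, depending on the sign of the true changes.

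**4. The plan's own withdrawal figure**

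Sample size and blinding allows 20% withdrawal: 52 × 0.80 = 41.6, in line with the stated 42 per group. That is an overall allowance; no part of it is tied to the drug rule.

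**The case against.** The strongest reply is that this is loose drafting and that the safeguards already exist. A general permission followed by a named list is commonly read as rule and exception. The withdrawal sentence stands in a section about treatment during the study, so use on study is its more natural sense and ever having taken a drug is a strained one. The inclusion and exclusion windows concern partly different drugs and apply cumulatively. Final tests after withdrawal and an intention-to-treat primary analysis are both in the article, and no protocol can compel a scan.

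Much of this stands, and it rules out four stronger readings that a reader might infer:

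- **That withdrawal takes randomised women out of the primary outcome.** It does not do so automatically. Data management keeps the final tests for those who agree, and Data analysis keeps everyone assigned. The loss arises only when the scan is declined.
- **That the 3-month and 4–6-month windows contradict each other.** They can both be applied. The fault is the range, and the lack of alignment where they overlap.
- **That power falls by a definite amount.** The article gives no rate for these withdrawals and no BMD effect or standard deviation; the sample size rests on an effective rate. Carrying values forward also keeps all 52 per arm in the analysis, and zero changes alter the standard deviation as well as the mean.
- **That withdrawals will differ by arm because pain persists under sham.** The article names no ordinary analgesic as prohibited. Some listed drugs might be started because of symptoms, but most have no evident link to response.

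What the reply does not remove: precedence is unstated, the look-back is unstated, one window is a range, and the stated penalty is leaving the study. These are rules that the article itself lays down, not detail left to a fuller document.

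**Conclusion.** The point holds in a limited form and should be corrected. As written, the rules allow identical women to be handled differently, and they end study participation for a drug deviation. For a withdrawn woman who declines the final scan, the primary outcome becomes an imputed change of zero. That last step assumes that BMD is measured only before and after treatment, as the Primary outcome section says.

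The size is not known. It is the share of women who are both withdrawn under this rule and not scanned, and the article gives no basis for estimating it. Equal shares in both arms would shrink the BMD difference by that share, under the assumption stated in the working; unequal shares could bias it in either direction.

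**What to change.** - Reconcile the permission and the prohibition, and the look-back periods in the inclusion criteria, the exclusion criteria and the concomitant-treatment section, into one rule with single cut-offs. Which drugs and which periods is for the sponsor's clinicians.
- Apply use before the study as an eligibility check at screening, so that no woman is randomised and then removed for earlier use.
- For use that starts after randomisation, replace withdrawal from the study with: record the drug and its dates as a protocol deviation; keep the woman in study follow-up, with the end-of-treatment L1–L4 BMD as a scheduled assessment; analyse her as randomised; exclude her from the per-protocol set only. Whether study treatment continues is for the sponsor's clinicians.

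The cost is protocol wording and a screening checklist, with no new visits. There is a small downside: some BMD values in the intention-to-treat analysis will be measured while a woman is taking a listed drug. The recorded deviations would show how many.
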